## Methods

### Study design

The design of this study protocol follows CONSORT guidelines. This study will be conducted as a cluster randomized controlled trial that is a two-arm trial. Nursing homes will be considered as clusters, and nursing homes rather than individuals will be randomized [23]. The intervention (a comprehensive PU prevention programme) will be implemented on all residents and care staff in entire nursing homes in the experimental group, while the usual care will be carried out in entire nursing homes in the control group. Adoption of this cluster design ensures that members of the care staff will provide the usual care and deliver the intervention to residents from two distinct groups of nursing homes (Fig. 1).

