### Sample size

In a previous study, [9] the incidence of PUs dropped from 9.5 % to 6 % after the implementation of the programme, corresponding to an odds ratio of 0.60 [7, 8]. Based on these figures, 710 residents (355 per group) will be required for 80 % power at a significance level of 0.05. Assuming an intra-cluster correlation of 0.1 %, a total of 784 (392 per group) will be required. Based on a previous study, [8] we allow for a 20 % drop-out rate and a 90 % resident recruitment rate. We will thus need 1088 residents from eight for-profit NHs (544 residents per group). The capacity of each home should then be around 130 to 140. Based on a similar PU prevention programme for care providers [8] that increased staff knowledge and skills with a Cohen’s d of 0.95 and 1.13 respectively, a total of at least 36 care staff (18 per group) will be required to achieve 80 % power at a significance level of 0.05. Allowing for a 30 % drop-out rate and a 70 % staff recruitment rate, [8]. We estimated that at least 74 care staff (37 per group) from eight nursing homes will be required for this study.

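### The staff sample size has no allowance for clustering although homes are randomised, so the stated 80 % power for staff knowledge (a secondary outcome) is overstated at the stated minimum

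*Protocol article*

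**What the plan says.** The Study design section sets the unit of randomisation: "Nursing homes will be considered as clusters, and nursing homes rather than individuals will be randomized". Under Randomization, four homes go to each arm.

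The Sample size section treats residents and staff differently.

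- **Residents:** clustering is allowed for. "Assuming an intra-cluster correlation of 0.1 %, a total of 784 (392 per group) will be required", up from 710.
- **Staff:** the section starts from an earlier programme "that increased staff knowledge and skills with a Cohen’s d of 0.95 and 1.13 respectively" and states that "a total of at least 36 care staff (18 per group) will be required to achieve 80 % power" at the 0.05 level. The only further adjustment is "Allowing for a 30 % drop-out rate and a 70 % staff recruitment rate", which leads to: "We estimated that at least 74 care staff (37 per group) from eight nursing homes will be required for this study".

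No ICC or design effect is given for staff. The Statistical analysis section plans an independent t-test for knowledge and skills. It also plans a GEE over time that adjusts these outcomes for the cluster effect. Staff knowledge and skills are named as secondary outcomes under Study outcomes and measures.

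**The concern.** The staff calculation is printed in full, from effect size to final number, and it contains no clustering step. This is therefore not a detail left to a fuller document. It also sits badly with the rest of the article, which inflates the resident sample for clustering and intends to adjust the staff outcomes for it.

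Staff of one home share an employer and a workplace, and the Discussion names shortages of equipment and manpower as barriers in these homes. Some correlation within homes is therefore plausible. If it exists, 18 staff per group carry less information than 18 independent people. Even without it, a comparison of four homes with four homes has few degrees of freedom.

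At stake is the power statement for the knowledge hypothesis and, under further conditions, that for the skills hypothesis. A null result on knowledge could be read as evidence against the training when the comparison never had 80 % power.

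**Working it through.** **Inputs from the Sample size and Randomization sections.** d = 0.95 (knowledge) and 1.13 (skills); alpha 0.05, taken as two-sided because that reproduces the stated figure; power 80 %; 18 analysed per group; 30 % drop-out; 70 % recruitment; four homes per arm.

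**Assumed.** A staff ICC of 0 to 0.20, because the article gives none. Its only ICC, 0.001, is for residents.

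**Step 1: reproduce the plan's figure.** Normal approximation: n per group = 2(1.96 + 0.84)²/0.95² = 17.4, which rounds up to 18. Power at 18 is 81.3 % by this approximation and 79.1 % by the t-test with 34 df. Skills needs 13 per group by the same formula, so knowledge drives the 18.

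**Step 2: reproduce the inflation.** 36/(0.7 × 0.7) = 73.5, so 74. Forwards, 74 approached gives 74 × 0.7 = 51.8 recruited and 51.8 × 0.7 = 36.3 analysed. Per group, 37 × 0.49 = 18.1. Nothing is left over for clustering.

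**Step 3: add clustering at the stated minimum.** Staff per home m = 18/4 = 4.5. Design effect DE = 1 + (4.5 − 1) × ICC. Noncentrality = d × √(18/(2 × DE)), which is 2.85 for knowledge and 3.39 for skills when DE = 1.

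- Design effect alone: normal approximation.
- Design effect and few homes: noncentral t with 8 − 2 = 6 df.

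| Assumed ICC | DE | Knowledge, DE alone | Knowledge, 6 df | Skills, DE alone | Skills, 6 df |
|---|---|---|---|---|---|
| 0 | 1.000 | 81.3 % | 66.3 % | 92.4 % | 80.5 % |
| 0.01 | 1.035 | 80.0 % | 64.9 % | 91.5 % | 79.2 % |
| 0.05 | 1.175 | 74.8 % | 59.5 % | 87.8 % | 74.1 % |
| 0.10 | 1.350 | 68.9 % | 53.8 % | 83.1 % | 68.3 % |
| 0.20 | 1.700 | 58.9 % | 45.1 % | 73.9 % | 58.6 % |

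At the residents' ICC of 0.001, DE is 1.0035. Knowledge then has 81.2 % power on the design effect alone and 66.2 % on 6 df.

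**Step 4: staff needed with homes fixed.** With four homes per arm, recruiting more staff raises m. Setting n/(1 + (n/4 − 1) × ICC) = 18 gives n = 18(1 − ICC)/(1 − 4.5 × ICC).

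- ICC 0.05: 17.1/0.775 = 22.1, so 23 analysed per group.
- ICC 0.10: 16.2/0.55 = 29.5, so 30.
- ICC 0.20: 14.4/0.10 = 144.
- No solution from ICC = 1/4.5, about 0.22.

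Dividing the unrounded values by 0.49 gives about 45 (ICC 0.05) and 60 (ICC 0.10) staff to approach per group, against the planned 37. On 6 df the analysed number for knowledge is 26 per group at ICC 0, 35 at 0.05 and 61 at 0.10.

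**The case against.** The strongest reply is that the loss from correlation rests on an ICC nobody has documented. At the only ICC in the article the design effect is negligible. The 6-df figures come from a cluster-level small-sample view, whereas the plan is an individual-level GEE with repeated assessments. This stands in part. The two losses should be shown separately, and none of the percentages is the power of the planned longitudinal analysis, which cannot be computed from the article. The objection does not rescue the 80 % claim, because the 6-df loss needs no ICC at all. Adjusting for clustering in the GEE corrects the analysis but does not add power.

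A reader might also infer more than the article supports:

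- **That 18 is a rounding error because the exact t-test needs 19.** It is not: 17.4 rounds up to 18, and the difference is a choice of formula.
- **That both staff hypotheses are underpowered.** For skills this is conditional. Skills keeps 83 % at ICC 0.10 on the design effect alone and about 80 % on 6 df at ICC 0. It falls clearly short only when a non-trivial ICC meets 6 df, or when the ICC is well above 0.10.
- **That recruitment will end at 74.** The article gives 74 as a minimum, and Participant recruitment sets no cap. More staff may be enrolled, and power would then be higher than shown here.
- **That staff are trained home by home.** The Interventions section does not say how the sessions are divided among the four homes, so the point does not rely on it.

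**Conclusion.** The point holds for knowledge. The staff number is that of an individually randomised trial, and the stated 80 % power is overstated at the stated minimum of 36 analysed staff. On the design effect alone, power drops below 80 % once the ICC exceeds about 0.01. With 6 df it is at most about 66 % anywhere in the assumed range.

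These sizes rest on the assumed ICCs, 4.5 analysed staff per home, the stated effect sizes, and a single unadjusted two-group comparison. For skills the shortfall is conditional. A reader might take the point as a weakness of the trial's main result. It is not: the staff outcomes are secondary, and the power for the primary resident outcomes is not affected by this point.

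**What to change.** In the Sample size section:

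1. State an assumed range for the staff ICC.
2. Apply the design effect with homes fixed at four per arm, so that staff per home rises with the number recruited. Multiplying 18 by a design effect computed at 4.5 staff per home would understate the need.
3. Show the loss from the design effect and the loss from having eight homes (6 df) separately.
4. Restate the power for knowledge at the stated minimum and, conditionally on the ICC, for skills. Say that the figures refer to a single comparison and not to the longitudinal GEE.
5. Label 74 as staff approached, about 52 recruited and 36 analysed.

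This changes wording only. The price is a less favourable stated power for the staff outcomes.

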### Randomization

Randomization will be carried out after the written informed consent of all individual residents to participate this study has been obtained and the recruitment of residents from the eight nursing homes has been completed. The PI will assign each nursing home that has agreed to join the study a number of from one to eight. A trained RA using the random number generator will randomly assign four numbers to the experimental group and the remaining four numbers to the control group. In accordance with the randomized numbers, the PI will assign the eight nursing homes to the experimental or control groups.

### Blinding

Only the four trained RAs who will be responsible for data collection will be blind to the group allocation. The PI and the care staff in the eight nursing homes will not be blind to the group allocation.

### Statistical analysis

IBM SPSS Statistics 22 will be used to analyse the data. An intention-to-treat analysis will be adopted. Descriptive statistics such as mean or percentage will be used to summarize PU prevention knowledge and skills, and the prevalence and incidence of PUs. A chi-square test will be performed to compare the PU prevalence and PU incidence of residents between the two groups. An independent t-test will be adopted to compare the knowledge and skills of care staff between the two groups. Generalized estimating equation (GEE) will be used to compare the two groups in terms of their performance in the knowledge and skills tests, as well as in PU status over time, and to examine the groups by the time interaction effect, adjusting for the cluster effect and possible confounders. Significance will be set at a P value of < =0.05.

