The incidence of PUs is not only an indicator of the quality of institutionalized care; PUs can also have a significant negative impact on residents, care staff, and healthcare costs. PUs cause pain, [10] which affects every aspect of a sufferer’s life. It restricts a person’s physical and functional abilities, induces psychological distress, reduces a person’s social life, and leads to increased dependence and greater financial costs [11]. In NHs, the cost of the dressing materials and the nursing time spent on dressing PUs is considerable [12]. If hospital care is required for severe PU cases in NHs, the cost will be great, [13] given the long treatment time and great likelihood of complication in severe cases. Moreover, if NH residents admitted to hospitals have a concurrent diagnosis of PUs, this tends to lead to an increased use of hospital resources, increased nursing time, slow recoveries from the morbid condition, [14] and prolonged hospitalizations [15]. PUs have been rated the fifth most frequent cause of potentially avoidable hospitalizations [16]. Given the abovementioned negative impacts of PUs and the increasing number of older people in for-profit NHs, PU prevention care should be well-planned and carried out in such settings.

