### Hypotheses

The experimental group will have a lower incidence and prevalence of PUs than the control group at the end of the implementation of the protocol.The care staff in the experimental group will have more PU knowledge than the care staff in the control group at the 8^th^ week, and at the end of the implementation of the protocol.The care staff in the experimental group will have higher-level PU prevention skills than the care staff in the control group at the 8^th^ week, and at the end of the implementation of the protocol.

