### Participants

The clusters are nursing homes. There will be eight private for-profit NHs in Hong Kong. They will be those that have been classified as category A2 homes in the Enhanced Bought Place Scheme (EBPS) and eager to improve the pressure ulcer prevention care that they currently offer, have a capacity of around 130–140 beds, and have no PU prevention protocol in place. We believe that EBPS-A2 homes will represent the target population of for-profit private NHs in Hong Kong because they hire few or no professional nurses but are considered more motivated to improve the quality of the care that they provide than non-EBPS homes, and would perhaps therefore be more likely than the latter to comply with the protocol. The study sample will be the residents and care staff from the eight private for-profit NHs in Hong Kong. The residents will be those aged 60 or above and the care staff will include personal care workers (PCWs) and health workers (HWs) who provide direct care to residents.

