### Study outcomes and measures

The primary outcomes are the incidence and prevalence of pressure ulcers. The secondary outcomes are the care staff’s knowledge and skills on preventing pressure ulcers. These outcomes will pertain to the cluster and individual participant levels.

PU incidence and prevalence: The incidence of PUs will be assessed using the validated PU incidence form [6]. The form will record the numbers, locations, and stages of the PUs that are detected. The common PU sites are numbered from 1 to 36 on a body map. The identification of stages will be adopted from the guidelines of the European Pressure Ulcer Advisory Panel and the National Pressure Ulcer Advisory Panel [7]. The prevalence of PUs will be evaluated using the validated prevalence form [6].

PU prevention knowledge: In this study, the knowledge test, which demonstrated good internal consistency and content validity, [8] will be adopted to assess the care staff’s knowledge of PU. The test has 30 true-false items, with each correct answer allocated a score of one. The range of scores is from 0 to 30, and the total score is 30. A higher score indicates a higher level of knowledge of PU.

PU prevention skill level: The skill checklist, which has good content validity and internal consistency, [8] will be used to assess the care staff’s skills on turning, positioning, transferring, lifting, and use of materials/devices for preventing pressure ulcers. The checklist lists the steps required to demonstrate the five different skills and the rating for the performance of the skill in each step using a 4-point scale: unsatisfactory (1), barely satisfactory (2), satisfactory (3), and very satisfactory (4). A higher total score indicates better skill at preventing PUs.

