### Study procedures

The four trained RAs, who are registered nurses and will be blind to the group allocation, will collect the data. Each RA will be responsible for collecting the data for two nursing homes. The following data will be collected from both the experimental and control groups (Table 1). Immediately before (T0) the lecture, at the 8^th^ week (T1), and at the end of the implementation (T2) of the protocol (at the 16^th^ week of the implementation of the protocol), the staff participants will be assessed on their knowledge on preventing pressure ulcers in the presence of the RAs. Before the commencement of the skill training (T0), at the 8^th^ week (T1), and at the end (T2) of the implementation of the protocol (T3), the RAs will conduct an individual assessment of the staff participants’ skills on turning, positioning, transferring, lifting, and the use of preventive materials, while they are performing daily care for residents.

**Table 1 Tab1:** Data collection

Study outcomes	Before the lecture	Before the skill training	Immediately before commencement of protocol implementation	8^th^ week after the protocol	At the end of the protocol
Knowledge	✓			✓	✓
Skills		✓		✓	✓
Prevalence	✓		✓	✓	✓
Incidence “-------------------------------the whole period					

In assessing the incidence of PUs, the RAs will inspect the skin of each resident two times a week to detect the first PUs (on residents without PUs) and new PUs (on residents already suffering from PUs), starting from before the intensive training course to the end of the implementation of the protocol. The size, location, and stage of PUs will be assessed when they are detected. The prevalence of PUs will be evaluated by the RAs before the commencement of the intensive training course (T0), immediately before the commencement of the implementation of the protocol (T1), at the 8^th^ week (T2), and at the end (T3) of the implementation of the protocol. An inter-rater agreement of at least 90 % among four RAs will be obtained for the skill checklists and PU assessment (size, location, and stage) before the skill-training sessions.

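### The chi-square test of end-of-protocol prevalence ignores ulcers already present at T0 and ignores clustering, and the plan does not say whether it or the GEE decides the prevalence part of hypothesis 1

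*Protocol article*

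**What the plan says.** Study outcomes and measures: "The primary outcomes are the incidence and prevalence of pressure ulcers". The Hypotheses section sets the time point: "The experimental group will have a lower incidence and prevalence of PUs than the control group at the end of the implementation of the protocol".

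Residents with existing ulcers are not excluded. The criterion in Participants is age ("The residents will be those aged 60 or above"), and Study procedures states that incidence inspections also look for "new PUs (on residents already suffering from PUs").

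In the numbering that Study procedures uses for prevalence, surveys take place at T0 (before the training course), T1 (just before the protocol starts), T2 (week 8) and T3 (end of protocol).

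Statistical analysis gives two methods for ulcer outcomes. The first is: "A chi-square test will be performed to compare the PU prevalence and PU incidence of residents between the two groups". The second is a GEE for ulcer status over time, with a group-by-time interaction and adjustment for the cluster effect and possible confounders. The section does not rank them.

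**The concern.** An ulcer present at T0 and still open at T3 counts as a T3 case in either arm. It arose before the programme and so says nothing about prevention. A chi-square test on T3 prevalence counts it like a new ulcer.

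Two things follow. Background cases pull the ratio between the arms towards 1 and cost power. And because only eight homes are randomized, four to each arm, the arms may start with different prevalence. Whatever part of that difference has not healed passes into the T3 comparison and would be read as programme effect, or would hide one. Prevalence is named as primary, so this would be a primary result.

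**Working it through.** **Inputs from the protocol article.** Incidence of 9.5 % versus 6 %, intra-cluster correlation 0.001, and 392 residents per group after the clustering allowance and before the drop-out and recruitment allowances (Sample size). Eight homes, four per arm (Randomization). The plan's odds ratio can be checked: (0.06/0.94)/(0.095/0.905) = 0.61, against the stated 0.60. The corresponding risk ratio is 0.06/0.095 = 0.63.

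**Inputs not in the documents (assumed).** T0 prevalence 5-15 %, share still present at T3 30-70 % and equal in both arms, and every new ulcer still open at T3.

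**Dilution.** Let c = T0 prevalence × share persisting, and r = 0.095 (control) or 0.06 (experimental). Then T3 prevalence = c + (1 − c) × r.

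| T0 prevalence | Persisting | c | Control T3 | Experimental T3 | Ratio | Carry-over share of control cases |
|---|---|---|---|---|---|---|
| 5 % | 30 % | 0.015 | 10.9 % | 7.4 % | 0.68 | 14 % |
| 10 % | 50 % | 0.050 | 14.0 % | 10.7 % | 0.76 | 36 % |
| 15 % | 70 % | 0.105 | 19.0 % | 15.9 % | 0.84 | 55 % |

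The absolute difference hardly moves (3.3 points in the middle row against 3.5). The loss lies in the ratio and in the larger variance. With 392 per group, two-sided and ignoring clustering, chi-square power is about 45 % for 9.5 % versus 6 % and about 29 % for 14.0 % versus 10.7 %. That the first figure is below the plan's 80 % is a separate sample-size matter; only the drop is relevant here.

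With wider assumptions (T0 prevalence 5-25 %, 30-80 % healed, half to all new ulcers still open at T3), the prevalence odds ratio runs from 0.64 to 0.92, and carry-over is 10 % to 82 % of control cases.

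**Imbalance.** Take a 5-point T0 difference with half persisting and no programme effect. The spurious T3 difference is 0.05 × 0.5 × (1 − 0.095) = 2.3 points. At 30 % and 70 % persistence it is 1.4 and 3.2 points. With the programme effect present, control T0 at 10 % and half persisting, the T3 difference is:

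- experimental T0 15 %: 14.0 − 13.0 = 1.0 point;
- experimental T0 10 %: 14.0 − 10.7 = 3.3 points;
- experimental T0 5 %: 14.0 − 8.3 = 5.7 points.

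**How likely is such an imbalance?** At 10 % prevalence with 98 residents per home (392/4), the variance of the T0 difference is 2 × 0.10 × 0.90/392 × (1 + 97 × ICC).

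- Plan's ICC of 0.001: 0.000459 × 1.097, SD 2.2 points. Five points is then about 2.2 SD. A 1-SD imbalance moves T3 by 0.022 × 0.5 × 0.905 = 1.0 point.
- Assumed ICC of 0.05: 0.000459 × 5.85, SD 5.2 points. Five points is then about 1 SD.

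The Background reports incidence of 25 % in private homes of one district and 9.5 % in another, so homes may differ by more than an ICC of 0.001 implies. These are incidence figures, not prevalence.

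**The case against.** The strongest reply is that the plan already contains the answer. The GEE uses ulcer status over time from T0, includes group by time and adjusts for the home. A contrast of change from T0 deals with arm-level imbalance. This stands, and it would be wrong to say that the plan takes no account of T0. But the GEE and the chi-square are listed for the same outcome with no order of precedence, so hypothesis 1 could be decided on the chi-square alone. Group by time also does not remove persisting ulcers from the outcome.

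Second, incidence is the other primary outcome and the basis of the sample size, and it counts only first or new ulcers. The prevention question is therefore answered elsewhere. This stands too. A reader might infer that only new ulcers can answer hypothesis 1, but that hypothesis names prevalence in its own right, and total burden is a legitimate outcome.

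Third, the programme may act on existing ulcers. Interventions describes ulcer assessment, risk-factor measures and referral to other disciplines. Equal persistence in both arms is thus an assumption of the calculation, not a fact of the plan.

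Fourth, the Background remark ("given the long treatment time and great likelihood of complication in severe cases") concerns severe cases needing hospital care. It does not show that T0 ulcers in general last until T3, which lies more than 16 weeks after T0 because the training comes in between.

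Finally, a condensed article may leave precedence to a fuller plan. But the chi-square is a stated choice here, not a gap.

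**Conclusion.** The point holds in limited form. T3 prevalence combines old and new ulcers, and the stated chi-square compares it with no term for T0 status or home. Dilution is partial: the ratio is 0.68-0.84 instead of 0.63 under the main assumptions. A 5-point T0 imbalance would shift the T3 difference by 1.4 to 3.2 points in either direction. The 3.5-point yardstick is an incidence difference, since the plan states no expected prevalence difference.

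A reader might infer that T3 prevalence is mostly old disease. The documents do not support this. They give neither a prevalence nor a healing rate, and carry-over is 14-55 % of control cases in the main range, a minority in most of it. If some new ulcers heal before T3, the share rises; if more T0 ulcers heal, it falls.

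This is an inexpensive improvement to how one primary outcome is tested. It does not undermine the trial's ability to assess prevention.

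**What to change.** State in Statistical analysis that the prevalence part of hypothesis 1 is tested by a GEE for ulcer status at T3 with home as the cluster and the resident's T0 ulcer status as a covariate. Alternatively, name the group-by-time contrast from T0 to T3 specifically, rather than an overall interaction across all four surveys. Keep raw T3 prevalence by arm as descriptive and drop the chi-square as a deciding test for it.

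Neither form removes old ulcers from the outcome. The covariate form compares residents with like T0 status, and the contrast form removes arm-level differences at T0. New ulcers remain the business of the incidence outcome.

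The cost is wording: the T0 survey is already scheduled and the GEE already planned. The downside is that a resident without a T0 survey needs a stated rule for baseline status. With eight homes, the model-robust standard errors also need care, as they do for the GEE already planned.

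A further report restricted to body sites clear at T0 is not recommended as things stand. The map ("The common PU sites are numbered from 1 to 36 on a body map") is described with the incidence form only, so location at the T0 survey is not shown to be recorded, and the result would largely duplicate incidence.

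### The protocol plans an unadjusted chi-square test and t-test beside a cluster-adjusted GEE, and names PU incidence expressly only under the chi-square

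*Protocol article*

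**What the plan says.** The Study design section makes the home the unit of allocation: "Nursing homes will be considered as clusters, and nursing homes rather than individuals will be randomized". Under Randomization, a research assistant will "randomly assign four numbers to the experimental group and the remaining four numbers to the control group". The outcomes section ranks the endpoints: "The primary outcomes are the incidence and prevalence of pressure ulcers", and "The secondary outcomes are the care staff’s knowledge and skills on preventing pressure ulcers".

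The Sample size section carries the clustering into the resident calculation. It assumes an ICC of 0.1 % and raises the requirement from 710 to 784 residents. It applies no ICC to the staff calculation.

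The Statistical analysis section then plans two layers of comparison:

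- Plain two-group tests. For residents: "A chi-square test will be performed to compare the PU prevalence and PU incidence of residents between the two groups". For staff: "An independent t-test will be adopted to compare the knowledge and skills of care staff between the two groups". No cluster adjustment is attached to either.
- A GEE that compares the groups on knowledge and skills, "as well as in PU status over time, and to examine the groups by the time interaction effect", with adjustment for the cluster effect and possible confounders.

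One significance threshold, P of 0.05 or less, is given for all of these.

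**The concern.** An ordinary chi-square test and an independent t-test take each resident or staff member as a separate, independent observation. In this trial the independent units are the eight homes. People in one home share staff, equipment and routines, so their outcomes tend to be alike. With any positive ICC the ordinary standard error is too small and so is the P value. The protocol accepts this premise when it inflates the resident sample size, then names tests that set it aside.

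The gap is sharpest for incidence, a primary outcome and the one from which the resident sample size is derived. It is named expressly only under the chi-square. The GEE refers to PU status over time, which fits prevalence readily: Table 1 shows prevalence measured at four time points and incidence recorded across the whole period. Whether PU status is meant to cover incidence is not stated.

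At stake is the false-positive rate of the main result. As written, a chi-square P value just under 0.05 could be reported as confirming the first hypothesis although an analysis that respects the randomisation would not support it.

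**Working it through.** **Inputs from the protocol article.** Eight homes, four per arm; 784 residents after cluster inflation, so 784 / 8 = 98 per home; ICC 0.001; 36 staff before allowances, so 36 / 8 = 4.5 per home; control incidence 9.5 %; threshold 0.05. I take the tests as two-sided, which the protocol does not state.

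**The protocol's own inflation.** Design effect DE = 1 + (m − 1) × ICC. With m = 98, DE = 1 + 97 × 0.001 = 1.097, and 710 × 1.097 = 779, against the stated 784. The stated figure corresponds to about 105 residents per home: (784 / 710 − 1) / 0.001 + 1 = 105. The agreement is close enough to confirm that the ICC was applied in this way. Then 784 / (0.8 × 0.9) = 1089, against 1088.

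**True size of a nominal 5 % unadjusted test.** The real variance is DE times the variance assumed, so the actual rejection rate under no effect is 2 × [1 − Φ(1.96 / √DE)].

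Chi-square, 98 residents per home:

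| ICC | DE | 1.96 / √DE | True type I error | Simulated |
|---|---|---|---|---|
| 0.001 (protocol) | 1.097 | 1.871 | 0.061 | 0.060 |
| 0.01 (assumed) | 1.97 | 1.396 | 0.163 | 0.164 |
| 0.02 (assumed) | 2.94 | 1.143 | 0.253 | 0.257 |

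The simulation drew 40,000 beta-binomial trials with 4 versus 4 homes, 98 residents each and 9.5 % incidence in both arms. At the full 136 per home (1088 / 8), the formula gives 0.066 at ICC 0.001 and 0.201 at 0.01.

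Staff t-test, 4.5 per home (normal approximation; all ICCs assumed, since the protocol gives none for staff):

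| ICC | DE | True type I error |
|---|---|---|
| 0.05 | 1.175 | 0.071 |
| 0.10 | 1.35 | 0.092 |
| 0.20 | 1.70 | 0.133 |

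**Candidate replacements.** In the same simulation, over ICCs from 0 to 0.05, a t-test on the eight home-level values (6 df) rejected in 4.5 % to 5.1 % of null trials. A simplified version of a GEE test, with an uncorrected sandwich variance and a normal reference, rejected in about 13 % to 14 %. With eight homes, cluster adjustment alone is therefore not enough; it needs a small-sample correction.

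**Power cost.** Take 392 per arm, 9.5 % versus 6 % and ICC 0.001. The unadjusted standard error is √[(0.095 × 0.905 + 0.06 × 0.94) / 392] = 0.0191; multiplied by √1.097 it is 0.0200. The standardised difference is 0.035 / 0.0200 = 1.75.

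| Test | Critical value | Power |
|---|---|---|
| Unadjusted test, as it would be computed with no clustering | 1.96 | about 45 % |
| Cluster-adjusted, normal reference | 1.96 | about 42 % |
| Home-level t, 6 df | 2.45 | about 32 % |
| Home-level t, 5 df, before any gain from a covariate | 2.57 | about 30 % |

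All of these lie well below 80 %, even the first, because the stated 355 per group does not reproduce for 9.5 % versus 6 %. That is a separate matter. What counts here is the difference between the rows.

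**The case against.** The strongest reply is that clustering is handled. The GEE is a between-group comparison that adjusts for the cluster effect and covers knowledge, skills and PU status. Knowledge, skills and prevalence are all measured repeatedly, so it suits them well. This stands: a reader might infer from the chi-square and t-test sentences that the trial's group comparisons ignore clustering altogether, and the text does not support that.

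Second, the article condenses a fuller protocol, and ranking crude and adjusted analyses is commonly left to the SAP. This also stands: silence about which analysis decides would not be a finding by itself. The point rests on what is stated, namely tests named for between-group inference that do not suit the design.

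Third, the inflation is small at the only ICC given, about one percentage point. This stands as well. A reader might take the 16 % or 25 % figures as the expected error; they depend on ICCs ten and twenty times the protocol's value. The Background does report incidence of 25 % in four private homes in one district and 9.5 % in three in another, while ICC 0.001 at 9.5 % implies a between-home standard deviation of only √(0.001 × 0.095 × 0.905) = 0.93 percentage points. Those are separate studies and no estimate of the ICC, but they make it prudent not to rely on 0.001.

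The reply does not explain why unsuitable tests should be used for inference at all, nor does it place incidence under the GEE.

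**Conclusion.** The concern holds in limited form. The chi-square and t-test, as named, do not respect the randomised unit and conflict with the protocol's own ICC allowance. They stand beside a cluster-adjusted GEE at the same threshold, and incidence is expressly assigned only to the chi-square.

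The size depends on the ICC. At the stated 0.001 the chi-square's error is about 6 % instead of 5 %, which is minor; it becomes serious only if homes differ more than the protocol assumes. The staff figures rest wholly on assumed ICCs. All figures assume equal home sizes and two-sided testing.

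The documents do not show that the trial lacks a cluster-valid analysis, nor that its error rate will be as high as the upper figures. They show that a wrongly chosen test is written into the plan for the primary outcomes and can be removed at little effort.

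**What to change.** Drop the chi-square and t-test as inferential tests, or keep the crude group summaries as descriptive only, without P values. State that a cluster-valid analysis decides each of the four outcomes, and name incidence in that sentence. Either of two routes would serve:

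- the planned GEE, with a small-sample correction stated for eight homes; or
- a comparison of the 4 versus 4 home-level values (incidence, prevalence, mean knowledge, mean skill) by a t-test with 6 df, or 5 df if adjusted for one home-level baseline value.

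The change is one of wording and needs no new data. The downside is wider intervals and lower power than the unadjusted tests appear to give: at 392 per arm and ICC 0.001, about 32 % with 6 df against an apparent 45 %. A baseline covariate may recover some precision but costs one of the six degrees of freedom.
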